## Abstract

**Introduction:**

School-based active mile initiatives such as The Daily Mile (TDM) are widely promoted to address shortfalls in meeting physical activity recommendations. The iMprOVE Study aims to examine the impact of TDM on children’s physical and mental health and educational attainment throughout primary school.

**Methods and analysis:**

iMprOVE is a longitudinal quasi-experimental cohort study. We will send a survey to all state-funded primary schools in Greater London to identify participation in TDM. The survey responses will be used for non-random allocation to either the intervention group (Daily Mile schools) or to the control group (non-Daily Mile schools). We aim to recruit 3533 year 1 children (aged 5–6 years) from 77 primary schools and follow them up annually until the end of their primary school years. Data collection taking place at baseline (children in school year 1) and each primary school year thereafter includes device-based measures of moderate-to-vigorous physical activity (MVPA) and questionnaires to measure mental health (Strengths and Difficulties Questionnaire) and educational attainment (ratings from ‘below expected’ to ‘above expected levels’). The primary outcome is the mean change in MVPA minutes from baseline to year 6 during the school day among the intervention group compared with controls. We will use multilevel linear regression models adjusting for sociodemographic data and participation in TDM. The study is powered to detect a 10% (5.5 min) difference between the intervention and control group which would be considered clinically significant.

**Ethics and dissemination:**

Ethics has been approved from Imperial College Research Ethics Committee, reference 20IC6127. Key findings will be disseminated to the public through research networks, social, print and media broadcasts, community engagement opportunities and schools. We will work with policy-makers for direct application and impact of our findings.

Strengths and limitations of this studyThis quasi-experimental study is the most comprehensive study to date to examine the longitudinal impact of The Daily Mile on children’s health.Including schools in Greater London will reflect the diverse multiethnic primary school population.Low response rates from school surveys may result in a biased sample.Attrition may affect precision of effect sizes and bias results.

## Introduction

Increasing physical activity during childhood is a global goal to improve health in the population and reduce the growing health risks from non-communicable diseases.^1 2^ Regular physical activity is associated with better cardiorespiratory and muscular fitness and bone health.^3^ A growing science base suggests links between children’s physical activity and psychological and social health including sleep, cognition, self-confidence and social interaction.^3^ This is particularly important in childhood where health behaviours may become embedded.^4^ The UK’s chief medical officers recommend that children and young people, aged 5–18 years, should engage in sport and physical activity for an average of 60 min or more every day.^5^ The latest national self-report activity figures for children and young people by Sport England showed that around 47% are meeting these targets in the UK while 29% participate in less than an average of 30 min a day.^6^

School-based active mile initiatives are widely publicised to address significant shortfalls in children’s physical activity.^7^ Schools are considered ideal settings for physical activity initiatives given their wide reach.^8 9^ The Daily Mile (TDM) is a school-based active mile initiative that was launched in 2012 by a head teacher in Scotland, UK, who wanted to increase the fitness of her pupils.^10^ Since 2012, one in five schools in England are now registered with TDM^11^ and it has a growing global adoption.^12^ TDM is a teacher-led, free and simple initiative that involves children running or jogging for 15 min (‘a mile’) at least three times a week, in addition to national curriculum physical education (PE) and scheduled break times. TDM has been promoted in the UK’s Childhood Obesity Plan as an easy and accessible way to increase children’s physical activity during the school day to improve their fitness, health and well-being.^13^ As schooling is compulsory for all children in England, school-based active mile initiatives have the potential to reach all children, including those living in poverty, which may help to reduce the gap in physical activity among children.^14^

TDM appears to be reaching a nationally representative primary school population. Up to August 2019, 22% of all state-funded primary schools in England were registered, reaching a population of just over 963 000 children.^11^ The evolving evidence base of the benefits of TDM on physical activity is promising; a study by Chesham *et al*
15 showed an increase in children’s moderate-to-vigorous physical activity (MVPA) by approximately 9 min,^15^ and a study by Morris *et al*
16 demonstrated that during one active mile lesson, children accumulated between 5 and 15 min of MVPA. While there are acute assessments suggesting that children accumulate around an average of 10 min of MVPA during TDM, there is limited evidence of its impact on children’s mental health^17 18^ and inconsistencies on benefits to academic performance.^16 19^ Furthermore, some of the previous studies have focused on weight-related outcomes such as body fat and body mass index (BMI) and have reported conflicting results.^15 20^ TDM was not designed as an obesity prevention initiative and there is inconclusive evidence that increased physical activity alone is effective in preventing obesity in children.^21^ The evidence base still lacks an assessment of the impact and sustainability of TDM throughout primary school life.

A major gap in the evidence is the lack of data; there is limited evidence on how TDM is implemented in schools outside of experimental studies and limited follow-up times.^22–24^ Currently, there are no evaluations of the impact and sustainability of TDM throughout primary school life.

The iMprOVE Study will provide a robust real-world evaluation of the impact of TDM on children’s health, well-being and educational attainment over the course of primary school.

### Aims and research questions

The aim of the iMprOVE Study is to compare the change in MVPA of children in TDM schools with non-TDM schools across primary school years.

The following research questions will be addressed:

What is the difference in MVPA accumulated during the school day between children in TDM and non-TDM schools across primary school years?What are the differences in mental health and educational attainment of children in TDM and non-TDM schools across primary school years?How much MVPA is attributed to doing TDM and how much does this contribute to children’s overall physical activity?To what extent do primary schools in Greater London implement TDM according to its core principles?Are there any differential impacts of TDM on health in subgroups of children, schools and areas with greater health need?

## Methods and analysis

### Study design

The iMprOVE Study is a longitudinal quasi-experimental cohort study of state-funded primary schools located in Greater London which has a diverse multi-ethnic urban population. The target population is children in schools that participate in TDM (intervention group) compared with those that do not participate in TDM or any other active mile initiative (control group). We will assess children in the first year of primary school (aged 5–6 years) and follow them up annually in each successive primary school year until the end of primary school (year 6, children aged 10–11 years). In total, we will collect six waves of data (figure 1).

**Figure 1 F1:**
[figure not shown]
iMprOVE Study design.

### The intervention

TDM involves every child running or jogging at their own pace for 15 min, at least three times a week during the school day. TDM is in addition to curricular lessons including PE and scheduled break times. There are 10 core principles for successful delivery of TDM which schools are encouraged to follow (online supplemental table 1). These include that TDM should be conducted in all weathers and the full 15 min are spent on the activity without having to change clothing or shoes.^25^ TDM is also flexible to local adaptation by schools.

10.1136/bmjopen-2020-045879.supp1Supplementary data

Since 2017, we have held several professional and public multi-stakeholder consultations about which of the 10 core principles of TDM were essential criteria for successful implementation. The consultations included healthcare professionals, researchers and members from TDM Foundation. A consensus was reached agreeing a definition for school participation in TDM which was that three essential principles were adhered to: (1) the whole school takes part; (2) children are running or jogging for 15 min and (3) it is implemented at least three times a week.

### Procedure

#### School survey and recruitment

To identify which schools to assign to the intervention and control groups at baseline, we will send a school survey by post (including a link to the online version) with a freepost return envelope to all state-funded primary schools in Greater London (n=1721) derived from our database of primary schools in England.^11^ Any teacher who is best placed to answer questions about their school’s involvement with TDM can complete the survey. Schools that do not respond will be contacted by email 2 weeks after initial contact with a further email 1 week later. If required, we will conduct one further follow-up by phone to encourage survey completion 2 weeks after the second email. Responses from the survey will identify whether schools participate in TDM and if they do, how many of the 10 principles are adhered to. Schools which participate in the three essential principles of TDM identified from the public and expert consultation will be assigned to the intervention group and schools not participating in TDM or any other active mile initiative will be assigned to the control group. Primary schools where TDM is not implemented by the whole school will be considered ineligible for the study, for example, if they report only some classes or year groups take part, thus meeting only two of the three criteria considered essential (figure 2). We will contact the eligible schools to participate in the next stage of the study where through the schools, we will recruit year 1 primary school children (aged 5–6 years) and their parent/carer by letter and information sheet. For a child to be eligible to take part, their parent/carer will also need to agree to participate.

**Figure 2 F2:**
[figure not shown]
Identifying schools to be included in the iMprOVE Study.

#### Informed consent

Written and informed consent will be sought at the point of recruitment, prior to any data collection. We will first obtain consent from the headteacher of the school to allow the distribution of invitation letters to parents. Parents who agree to participate in the study will be emailed a consent form (for their participation), a parental consent form (allowing their child to participate) and a child assent form. Consent to take part in the study at baseline (Wave 1) will assume contact for subsequent follow-ups. At each follow-up, we will provide an option for participants to decline further participation.

### Outcomes and measures

We will collect data from children, parents and teachers which are detailed in online supplemental table 2.

10.1136/bmjopen-2020-045879.supp2Supplementary data

The main outcome is children’s mean MVPA minutes during the school day (we will match individual children to the start and end times of their school as reported by the teacher) measured using the GENEActiv (Activinsights, Cambridge, UK) wrist-worn accelerometers. The GENEActiv accelerometer is worn 24/7 including when in water and during sleep. Children will be instructed to wear the monitors for 24 hours on each day of a consecutive 7-day wear period. The accelerometers will be initialised for 9 days to obtain 7 full days of wear (excluding the date of issue and day of collecting the accelerometers). We will use raw acceleration data to classify wear time and assess time spent in activity intensities (including moderate, vigorous and MVPA). The threshold for identifying non-wear time will be based on reviewing the acceleration data and will follow a process to correct for diurnal bias similar to that used in previous studies.^26 27^ As the use and analysis of wrist-worn accelerometer data in younger age groups is still developing,^28 29^ we will review and adapt our process to reflect the updated knowledge and best practice at the time of first analysis. We will use segmented analysis to identify MVPA during TDM activities as reported by the class teacher, and to consider compensatory effects, we all assess minutes of MVPA during school hours and outside school hours and on weekdays overall and at the weekend.

The Strengths and Difficulties Questionnaire (SDQ), a measure of child mental health,^30^ is a brief behavioural screening questionnaire about children and young people aged from 2 years to 17 years. The SDQ has five subscales each including five items that assess emotional symptoms, conduct problems, hyperactivity, peer relationship problems and prosocial behaviour. It has been extensively validated^31^ and is one of the most widely and internationally used measures for assessing children’s mental health.^32^ Parent/carers and teachers will complete the SDQ about the child.

Educational attainment will be measured by teacher ratings of the child’s reading, writing and math ability on a 5-point Likert Scale ranging from 1 (below expected levels) to 5 (above expected levels).^20^ Ratings will be based on the UK’s National Curriculum’s ‘age related expectations’ which are the standard expectations defined by threshold descriptors indicating what pupils should be able to achieve by the end of primary school.^33^

#### Secondary outcomes

We will assess children’s self-reported (or completed by proxy) intensity of physical activity using the Children’s Physical Activity Questionnaire (C-PAQ).^34^ Collecting self-reported physical activity alongside accelerometer data will enable us to validate self-reported data with our objective measure of physical activity.

The Child Health Utility 9D (CHU-9D) will measure children’s health-related quality of life (HRQoL).^35^ The CHU-9D assesses how children are feeling ‘today’ by addressing nine items (worry, sadness, pain, tiredness, annoyance, problems with schoolwork, their daily routine and their ability to join in with activities). It is suitable for children aged from 7 years to 11 years and can be completed by proxy for younger children.^36^ The CHU-9D has good psychometric performance and shows potential as a valid and reliable instrument for measuring HRQoL.^37–39^

At baseline (children in school year 1) and at the first follow-up (children in year 2) the C-PAQ and CHU-9D will be completed by proxy about the child by the parent/carer. From school year 3 until the end of primary school, children will be encouraged to complete their own questionnaires with the help of their parent/carer (online supplemental table 2).

We will measure children’s height and weight from which we will calculate each child’s BMI as weight/height² (kg/m²) and standardised by age and sex.

#### Covariates

Parental physical and mental health is a strong predictor of child functioning.^40^ We will therefore collect parental self-reported physical activity, mental health, well-being and general health. The International Physical Activity Questionnaire-Short Form^41^ will measure time spent in different intensities of physical activity during the last 7 days. We will use the Warwick and Edinburgh Mental Wellbeing Scale which includes 14 items of feeling and functioning aspects of well-being to measure parental mental health.^42^

We will collect sociodemographic data on children’s date of birth, sex and ethnic group and parental sociodemographic data including age, sex, ethnic group, highest level of qualification and employment status. These data will be collected through questionnaires completed by the parent/carer. For the covariates of age/date of birth, sex and ethnic group of the children and parent/carer, the questions will only be included at baseline. Parent/carer qualification and employment data will be asked at each follow-up stage as these could change throughout the study period.

School characteristics including school size (ie, overall pupil numbers), class size, ethnic composition, area level of deprivation and number of pupils eligible for free school meals will be obtained from publicly available data provided by the Department of Education. School participation in TDM will be sought at the start of each follow-up data collection.

### Data collection

We will email a link to the questionnaires to parent/carers and class teachers. Paper versions will be available on request. Parents will complete the child questionnaires by proxy.

The iMprOVE research team will arrange a convenient time to visit the school to take anthropometry measures of the children and issue and fit them with the accelerometer. Verbal instructions of wearing the monitor will be given along with an information pack including details of wearing the monitor correctly, how long to wear and when and how to return the monitors. Incentives (shopping voucher) will be offered to the child to encourage successful completion of all their corresponding data collection.

All measures taken at baseline will be repeated at each follow-up. From Wave 3 onwards, the children (now in year group 3 and aged 7–8 years) will be encouraged to complete their own questionnaires with help from their parent/carer. Incentives for the children after each wave of data collection will be offered to encourage families to continue taking part.

### Data collection time points

There will be one data collection in each school year. Data collection for baseline (Wave 1) will begin from January 2021 (allowing for regular TDM activity to take place if implemented by the school) and will continue until we have met our sample size targets. Control group participants will be assessed simultaneously to the intervention group (figure 1).

For consistency and potential seasonal variation in activity levels, we aim to carry out follow-up assessments during the same month as baseline assessments in each year until the end of data collection in 2026 (figure 1).

### Sample size

Our sample size is based on the primary outcome of mean MVPA (minutes) per day allowing for the clustering of children in the same school and the primary analysis adjusting for baseline minutes of MVPA. Based on our previous work, there is an average of 46 children per state-funded primary school in Greater London.^11^

We conducted a sample size calculation (using STATA V.15.1) that produced a total sample of 3533 children (approximately 1767 children in the intervention and control groups) across 77 schools to give the study 90% power to detect a 5.5 min increase in the mean daily average MVPA minutes between children in TDM schools compared with non-TDM schools, assuming a mean daily average MVPA of 53 min (SD 22) in the control group based on the study by Chesham *et al*.^15^ This has been inflated to allow for 60% attrition across the follow-up period and assumes a two-sided alpha equal to 0.05. To allow for the analyses to include clustering at school level, we have applied an intraclass correlation coefficient of 0.05 to our calculation (online supplemental table 3). An increase of just over 5 min of MVPA per day equal to a 10% difference would be clinically significant to increase physical activity among the proportion of children who participate in less than an average of 30 min per day.

10.1136/bmjopen-2020-045879.supp3Supplementary data

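### The sample size is built on daily MVPA while the primary outcome is school-day MVPA, so power for a 10% (5.5 min) difference is not established for the primary outcome

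*Protocol article*

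**What the plan says.** The Abstract (Methods and analysis) gives the endpoint as follows: "The primary outcome is the mean change in MVPA minutes from baseline to year 6 during the school day among the intervention group compared with" the control group. Outcomes and measures agrees: "The main outcome is children’s mean MVPA minutes during the school day", with each child matched to the start and end times of their own school. The same section treats school hours as one of several separate quantities, since the team will also "assess minutes of MVPA during school hours and outside school hours and on weekdays overall and at the weekend".

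The Sample size section describes a different quantity. It opens with "Our sample size is based on the primary outcome of mean MVPA (minutes) per day" and continues by "assuming a mean daily average MVPA of 53 min (SD 22) in the control group", citing an earlier study of The Daily Mile. The target is a 5.5 min increase in that daily average, with 90% power, two-sided alpha 0.05, ICC 0.05, 46 children per school and an allowance for 60% attrition. Its clinical importance is argued from children who average under 30 min per day.

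Directly after defining the school-day outcome, the Abstract states: "The study is powered to detect a 10% (5.5 min) difference between the intervention and control group". The article gives no school-day mean, SD or ICC.

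**The concern.** School hours are only part of the day, so the mean, the SD and possibly the ICC of school-day MVPA will differ from the daily values. Three things are then carried over without support: the variance behind the sample size, the description of 5.5 min as a 10% difference, and the argument that such a difference matters clinically. That argument uses a whole-day benchmark; the Introduction reports the 30 min figure alongside the 60 min daily recommendation.

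At stake is how the primary result will be read. On a school-day mean well below 53 min, 10% and 5.5 min are two different targets. A reader could not tell which one the study was designed to detect, or which threshold of clinical significance applies.

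**Working it through.** **1. Reproduce the plan's figure from the daily inputs.** All inputs are from the Sample size section: SD 22, difference 5.5, two-sided alpha 0.05, power 90%, ICC 0.05, 46 per school, 60% attrition, equal groups.

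- Per arm, unclustered: 2 × (1.960 + 1.282)² × 22² / 5.5² = 2 × 10.51 × 16 ≈ 336.2, which gives 337 with rounding up.
- Design effect: 1 + (46 − 1) × 0.05 = 3.25.
- Per arm, clustered: 337 × 3.25 = 1095.25. Divided by 46 this is 23.8, so 24 schools, or 24 × 46 = 1104 children. Both arms: 2208.
- Attrition: 2208 × 1.6 = 3532.8, so 3533. Schools: 3533 / 46 = 76.8, so 77.

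Both published totals are recovered. The mean of 53 does not enter this formula; only the ratio of SD to difference does. The mean matters for the percentage. (Inflating by 1.6 rather than dividing by 0.4 is a separate matter and is not used here.)

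**2. Where 10% and 5.5 min coincide.** 5.5 / 53 = 10.4%, and 5.5 / 0.10 = 55. The two descriptions agree only for a control mean of about 53 to 55 min.

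**3. Move to school hours.** The article gives no school-day share. Assumption: school hours supply a fraction f of the 53 min, with f between 0.30 and 0.60.

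- Control mean: 53 × 0.30 = 15.9 min, to 53 × 0.60 = 31.8 min.
- 5.5 min as a percentage: 5.5 / 31.8 = 17%, to 5.5 / 15.9 = 35%.
- 10% in minutes: 1.6 to 3.2.

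**4. Power on the pre-inflation sample** (2208 children, 46 per school, ICC 0.05). SE = SD × √(2 × 3.25 / 1104) = SD × 0.0767, and power = Φ(difference / SE − 1.96). The school-day SD is unknown, so three cases are shown.

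| School-day SD | SD at f = 0.30 / 0.60 | Power for 10% at f = 0.30 / 0.60 | Power for 5.5 min |
|---|---|---|---|
| Shrinks with the mean (22f) | 6.6 / 13.2 | 88% / 88% | near 100% |
| Shrinks with √f | 12.0 / 17.0 | 40% / 68% | 99% or more |
| Stays at 22 | 22 / 22 | 15% / 47% | 90% |

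Two worked entries:

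- SD 22, f = 0.30: SE = 1.688; 1.59 / 1.688 = 0.942; Φ(0.942 − 1.96) = 0.15.
- SD 22, 5.5 min: 5.5 / 1.688 = 3.258; Φ(3.258 − 1.96) = 0.90.

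**5. Sensitivity to the sample used.** If 60% of the 3533 are lost evenly over 77 schools, 1413 children remain, about 18 per school. Power for 10% then runs from about 17% to 91%, and power for 5.5 min at SD 22 is 93%. The picture is unchanged.

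**The case against.** The best defence is that the design also states an absolute target of 5.5 min, and for that target the daily SD is probably conservative. This stands. With a school-day SD of 22 or less and an ICC of 0.05, power for 5.5 min is at least 90%. With SD 11 it is still about 96% at an ICC of 0.20: the design effect is 1 + 45 × 0.20 = 10, SE = 11 × √(20 / 1104) = 1.48, and Φ(5.5 / 1.48 − 1.96) ≈ 0.96. The planned baseline adjustment would add some power, and none of the figures above credits it. The 15% end also needs a school-day SD larger than its mean, so it is an outer bound.

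A reader might infer that the study is underpowered. One route is to take roughly 10 min per session (the Introduction reports that "children accumulate around an average of 10 min of MVPA during TDM") at the minimum of three sessions a week, and spread 30 min over seven days to get 4.3 min. That is not the primary-outcome scale. Over five school days the same dose, if fully additive, is 6.0 min, which exceeds 5.5. Three sessions is also a minimum. The opposite inference, that the sample is several times too large, needs the SD to shrink with the mean and the ICC to stay at 0.05; the article supports neither.

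It is also fair to say that 10.4% is reasonably rounded to 10%, so 5.5 against 5.3 min is no error. Finally, the source of the 53 min is not at hand, nor is the supplemental table of the calculation. Whole-day is the natural reading of a daily average justified by a 30 min per day benchmark, but it is not confirmed. If the figure was meant for school hours, the Sample size wording and its rationale still need correcting.

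**Conclusion.** The point holds as an inconsistency between the defined primary outcome and the outcome used for the sample size; the arithmetic itself reproduces. The Abstract's claim of power for a 10% (5.5 min) difference is not established for school-day MVPA, because the two descriptions part company at any mean well below 53 min. With school hours at 30–60% of daily MVPA, 5.5 min is 17–35% of the control mean, and power for a true 10% difference lies between about 15% and 88%. That range rests on the assumed share, on an ICC of 0.05 and on an SD between proportional shrinkage and no shrinkage. The documents do not show too little power for an absolute 5.5 min. What is missing is a supported statement of which difference, on the school-day scale, the study is designed to detect.

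**What to change.** Keep school-day MVPA as the primary outcome. Restate for school hours the control mean, SD, ICC, target difference (in minutes with its matching percentage), clinical rationale and resulting power. Existing accelerometer data, or Wave 1 data pooled and masked to group, can supply the mean, SD and ICC.

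If the daily scale is kept for planning, say in both the Abstract and the Sample size section that the power figure refers to whole-day MVPA, which is not the primary outcome, and remove 10% as a description of the school-day target. The article does not list whole-day MVPA among its secondary outcomes, so it should not be given that label in passing.

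The cost is a recalculation and rewording of two sections, plus the supplemental sample size table if it carries the same inputs. Recruitment does not change. The one downside is that the stated power for a 10% difference may turn out less favourable.

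### The 60% attrition allowance appears to have been applied as n × 1.6 rather than n / 0.4; whether 90% power survives 60% loss then depends on whether children or whole schools are lost

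*Protocol article*

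**What the plan says.** The Sample size section of the protocol article says that the calculation "produced a total sample of 3533 children (approximately 1767 children in the intervention and control groups) across 77 schools". The target is 90% power for a 5.5 min difference in daily MVPA. The control-group figures are introduced with the words "assuming a mean daily average MVPA of 53 min (SD 22) in the control group". On cluster size it says that "there is an average of 46 children per state-funded primary school in Greater London", and it applies an intraclass correlation of 0.05. On loss to follow-up it says: "This has been inflated to allow for 60% attrition across the follow-up period and assumes a two-sided alpha equal to 0.05".

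The same section says that the calculation allows for adjustment for baseline MVPA, but the text prints no baseline-to-follow-up correlation. It prints neither the number before inflation nor the inflation formula. The detail is referred to online supplemental table 3, which is not among the documents reviewed.

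**The concern.** If a fraction d of participants is lost, 1 − d remain, so the number needed at analysis is divided by 1 − d. Multiplying by 1 + d is a common slip. At small d the two nearly agree, but at d = 0.6 the factors are 2.5 and 1.6. The published total matches the smaller factor.

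Attrition is one of the two limitations that the article lists for itself under its strengths and limitations. Follow-up runs over six annual waves. Under Data collection time points, baseline collection continues until the sample size targets are met, so 3533 and 77 act as the stopping point for recruitment. A team that believes a 60% loss is fully covered may give too little attention to keeping schools in the study, which is where the power is most exposed.

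**Working it through.** **Inputs** (all from the Sample size section): difference 5.5 min; SD 22; power 90%; two-sided alpha 0.05; equal groups; 46 children per school; ICC 0.05; attrition 60%. No baseline-correlation gain is included, because no correlation is printed.

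**Reproducing the published figures**

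1. Per arm, unclustered: 2 × (1.960 + 1.2816)² × (22/5.5)² = 336.2.
2. Design effect: 1 + (46 − 1) × 0.05 = 3.25.
3. Per arm, clustered: 336.2 × 3.25 = 1092.8, or 1092.8/46 = 23.8 schools, rounded up to 24.
4. Total before inflation: 48 schools × 46 = 2208 children.
5. Inflation, two ways:

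| Operation | Children | Schools (children/46) |
|---|---|---|
| 2208 × 1.6 | 3532.8 → 3533 | 76.8 → 77 |
| 2208 / 0.4 | 5520 | 120 |
| Published | 3533 | 77 |

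The first row matches both published figures with no free parameter. Without rounding to whole schools at step 3, the multiplication gives 3497 and the division 5464; the division still does not match. Nor do variants of the division: one-sided alpha gives 4453, 80% power 4081, and a 5.3 min difference 5884.

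The published numbers point the same way. 3533 is not a multiple of 46 (77 × 46 = 3542), and 77 does not split equally between two arms. A multiplier applied after rounding to whole schools would leave that trace.

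**Attrition covered at the design effect used**

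- 1 − 2208/3533 = 37.5%.
- After 60% loss: 3533 × 0.4 = 1413 children, and 1413/2208 = 64% of the number needed.

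**Power after 60% total loss, by pattern of loss**

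With K schools left and m children in each, SE = sqrt(4 × 22² × (1 + (m − 1) × 0.05)/(m × K)), and power = Φ(5.5/SE − 1.960). In every row m × K = 1413.

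| Pattern | K | m | Design effect | SE | Power |
|---|---|---|---|---|---|
| Children lost evenly, all schools stay | 77 | 18.4 | 1.87 | 1.60 | 93% |
| 30% of schools leave, remaining loss among children | 53.9 | 26.2 | 2.26 | 1.76 | 88% |
| Half of schools leave, remaining loss among children | 38.5 | 36.7 | 2.79 | 1.95 | 80% |
| Whole schools only | 30.7 | 46 | 3.25 | 2.11 | 74% |

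With a t reference on K − 2 degrees of freedom, the first row is 92% and the last 71%. In the first pattern, power stays at or above 90% up to about 67% attrition.

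**The case against.** **The multiplication is inferred.** The article does not print the formula, and supplemental table 3 might show another route. Because baseline adjustment is said to be allowed for, a variance factor of 1 − r² with r = 0.6 followed by a correct division gives the same multiplier: 0.64/0.4 = 1.6. This cannot be excluded, but it fits less directly. If the factor is applied before rounding to whole schools, 336.2 × 0.64 × 3.25 = 699.4 per arm, or 15.2 schools, rounded up to 16. Then 32 × 46 = 1472, and 1472/0.4 = 3680 children in 80 schools. Unrounded, the route gives 3497. It gives 3533 only if schools are first rounded to 24 per arm without the correlation and the factor is applied afterwards.

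**The consequence is conditional.** A reader might infer that the study needs 5520 children in 120 schools, or that 3533 is simply too few. The documents do not support that. Those figures require a design effect held at 3.25 and no gain from baseline adjustment. If children are lost within schools, m falls to 18.4 and the design effect to 1.87. The number needed at analysis is then 2 × 336.2 × 1.87 = 1258, and 1258/0.4 = 3144 children (3220 in 70 schools with equal arms), which is below 3533. For the same reason, 37.5% is not a general limit.

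**The loss described is mostly of families.** The Informed consent section lets participants decline at each follow-up, and the Data collection section offers incentives to keep families taking part. Schools that stop or start the intervention are handled in sensitivity analyses and are not described as lost. The 74% case therefore needs an extreme pattern. Baseline adjustment would also help: with an assumed r of 0.5 or 0.6, power in that case is about 85% or 90%, and with r = 0.3 the 88% case exceeds 90%. This stands as a reason for moderation. It does not remove the point, because school withdrawal is not ruled out and no correlation is stated.

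**Conclusion.** On the printed inputs, the published total and number of schools are those of n × (1 + 0.6), so the 60% allowance appears to be misapplied. At 46 children per school and with no baseline-correlation gain, the sample covers 37.5% attrition. At 60% loss, the 90% power claim holds if schools stay and children are lost evenly (about 93%). It weakens as whole schools leave: about 88%, 80% and 74% (71% on t) in the patterns worked above. The statement should be corrected, but the design does not fail because of it. The conclusion rests on the printed inputs being those actually used, and supplemental table 3 could change the explanation. Even then, the paragraph would need to state the baseline correlation on which its total depends.

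**What to change.** In the Sample size section and supplemental table 3, state the number before inflation, the inflation formula, and any baseline-to-follow-up correlation used. If the formula was n × 1.6, do one of the following:

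- Restate the allowance as 37.5%, explicitly conditional on a fixed 46 children per school.
- Keep 60% and restate power from schools retained × children per retained school, giving child-level and school-level attrition separately.

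If 5520 children in 120 schools is mentioned at all, label it as conditional on a fixed design effect and no baseline-correlation gain, not as a required sample.

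The cost is rewording one paragraph and one supplementary table. No extra recruitment and no change to the analysis are needed. The downside is that the stated allowance or power may look less favourable.
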